### Objectives

The SOOTHE (Study of Mānuka Honey for Digestive Health) feasibility study aims to gather information required to design and undertake future clinical trials investigating the effect of Lepteridine-standardized mānuka honey on FD. The primary objective is to assess the effect of 6-week consumption of Lepteridine-standardized mānuka honey on symptom severity and quality of life in FD. This will be measured by changes in global Nepean Dyspepsia Index (NDI) scores from baseline to the end of the intervention. Data on recruitment time frame, strategies to improve recruitment, potential issues with adherence and attrition, and strategies to optimize adherence shall also be collected.

Secondary objectives include examining changes in Patient-Reported Outcome Measurement Information System (PROMIS gastrointestinal, anxiety, and depression) scores, immune parameters, and the gut microbiota composition between the Lepteridine-standardized mānuka honey and control groups. The study will also explore the pharmacokinetic profile of Lepteridine and other mānuka honey–derived metabolites in plasma and urine following acute consumption of Lepteridine-standardized mānuka honey.

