### Outcome Measurements

#### Primary Feasibility Measurement

The primary feasibility outcomes are changes from baseline to week 6 in FD symptoms and FD health-related quality of life, which were assessed using the NDI questionnaire. This is a validated instrument with a 2-week recall that evaluates the severity of symptoms and its impact on quality of life [48].

The symptom instrument of the NDI consists of 15 common dyspeptic symptoms that are rated using a Likert scale that evaluates the frequency, intensity, and bothersomeness of each symptom. The scores for frequency, intensity, and bothersomeness are summed to give a score for each symptom with a possible score range of 0 to 13. Higher scores represent greater symptom severity. The total symptom score is calculated as the sum of scores for all 15 individual symptoms and can range from 0 to 195. The total symptom scores are not scaled to 100, and no minimum clinically important difference (MCID) has been established [49].

The quality-of-life component of the NDI includes 25 questions that are summed to form a global score and scores for 4 subscales (or domains) measuring the impact of the condition on enjoyment of life and emotional well-being, lack of knowledge and control over the illness, disturbance to eating or drinking, and disturbance to sleep. The scores are scaled to 100 and are sometimes reversed so that high scores indicate better quality of life [50]. The quality-of-life scales can also be weighed to rank the importance of the domain to the respondent. An MCID of 10 points has been established for the NDI-weighted quality-of-life instrument [48].

In addition to changes in mean scores, responder analyses will be conducted based on the percentage of participants who demonstrated improvement in NDI scores from baseline to follow-up of 10%, 20%, 30%, and 40% for symptom severity, and 10, 20, and 30 points for quality of life. Furthermore, the percentage of participants reporting an improvement equal to or exceeding the MCID for quality of life will be compared between the groups. Effect sizes and SDs in symptom changes and quality of life between and within groups will help identify key outcome measures and sample sizes required for future studies.

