#### Statistical Analyses

All statistical analyses will be done using either R (version 4.3.2), Stata/SE version 18.0, or IBM SPSS version 29. The primary outcome analyses will use the intention-to-treat population (ITT) and per-protocol population. Secondary and exploratory analyses will be conducted with the ITT population. The ITT population will include all randomized participants who took at least 1 dose of the intervention. The per-protocol population will include those in ITT who had no major protocol violations, had all the study assessments required to analyze any outcome, and consumed at least 80% of their intervention product. Participants with missing data for a relevant outcome assessment will be imputed using the last observation carried forward.

The primary analysis will compare the overall NDI score changes for symptom severity and quality of life from baseline to week 6. Quality of life scores weighted by the participants’ perception of importance and unweighted scores will be examined. A general linear model that includes the randomized group as a fixed factor will be used (unadjusted results), and models adjusting for baseline values will also be presented. The residual plots from these analyses will be visually inspected, and if reasonable normality is not apparent, alternative generalized linear models will be undertaken.

For the secondary outcomes, changes in scores from baseline to the end of the intervention will be analyzed using appropriate statistical tests, depending on the data distribution. Descriptive statistics will be presented as frequencies, percentages, and mean (SD) for normally distributed parameters or medians (IQRs) for non-normally distributed parameters with a 95% CI and *P*≤.05 value to show statistical significance. Appropriate statistical techniques shall be used to mitigate any potential confounders and shall be reported in subsequent publications of this study. No formal hypothesis testing will be conducted on these variables.

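### The primary analysis leads with an unadjusted change score and does not rank the quality-of-life version or the analysis population; two labels, 'global' and 'follow-up', also need correcting.

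*Protocol article*

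**What the plan says.** **Score.** The Objectives section names symptom severity and quality of life as the primary objective and adds: "This will be measured by changes in global Nepean Dyspepsia Index (NDI) scores from baseline to the end of the intervention". Under Primary Feasibility Measurement, the term global belongs to one part of the instrument only: "The quality-of-life component of the NDI includes 25 questions that are summed to form a global score". Symptoms have their own total, from 0 to 195. The minimum clinically important difference (MCID) of 10 points applies to weighted quality of life; none is established for the symptom total. The Statistical Analyses section uses a third term: "The primary analysis will compare the overall NDI score changes for symptom severity and quality of life from baseline to week 6". It continues: "Quality of life scores weighted by the participants’ perception of importance and unweighted scores will be examined".

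**Time point.** The primary outcomes run to week 6: "The primary feasibility outcomes are changes from baseline to week 6 in FD symptoms and FD health-related quality of life". The responder analyses under the same heading count "improvement in NDI scores from baseline to follow-up of 10%, 20%, 30%, and 40% for symptom severity". Study Overview uses follow-up for the final two weeks after the intervention, and Table 2 attaches the label to week 8.

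**Model and population.** The unadjusted group comparison "will be used (unadjusted results), and models adjusting for baseline values will also be presented". Both the intention-to-treat (ITT) and per-protocol populations are used for the primary outcome, with no order given.

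**Use of the result.** Sample Size gives estimation of the SD and potential effect size for the primary outcome as the reason for 75 participants. Primary Feasibility Measurement says that SDs of the changes will help set future sample sizes.

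**The concern.** This study's product is an SD and an effect size for the next trial, together with a judgement on whether that trial is worth running. Which score, population and model supplies those figures is therefore the main decision in the analysis. The plan leaves the quality-of-life version and the population open, and it puts the less efficient model first.

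Two things are at stake. The most favourable of several overlapping results could be emphasised as the primary one. And an SD taken from unadjusted changes would oversize a later trial that adjusts for baseline.

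The two labels add ambiguity. Read literally, *global* leaves symptoms without a primary measure in the Objectives. Read literally, *follow-up* moves the responder analyses to a questionnaire whose two-week recall lies wholly after the product has stopped.

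**Working it through.** **1. The plan's own figure.** The total of 75 has no numeric precision target, so it cannot be reproduced. The precision it gives can be computed. The 95% CI for an SD multiplies the estimate by √(df/χ²). With 75 participants in three groups (72 df) the factors are 0.860 to 1.195. With the 68 analysed (65 df) they are 0.854 to 1.207.

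**2. Number of primary results.** The inputs, all from Statistical Analyses, are:
- 3 scores (symptoms, weighted and unweighted quality of life)
- 2 populations
- 2 models

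An overall group test gives 3 × 2 × 2 = 12. Two honey-versus-control contrasts give 12 × 2 = 24. The responder analyses come on top.

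**3. Unadjusted against adjusted contrast.** Let σ be the SD at baseline and at week 6 (assumed equal) and r their correlation. The documents give neither, so r is shown over a range.
- Variance of a change: 2σ²(1−r)
- Residual variance after baseline adjustment: σ²(1−r²)
- Ratio, adjusted to change: (1+r)/2
- Oversizing factor if the change SD is used for an adjusted trial: 2/(1+r)

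| r | Variance ratio | SD ratio, change to adjusted | Oversizing factor |
|---|---|---|---|
| 0.3 | 0.65 | 1.24 | 1.54 |
| 0.5 | 0.75 | 1.15 | 1.33 |
| 0.7 | 0.85 | 1.08 | 1.18 |

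The direction does not depend on equal variances. With SDs σ₀ and σ₁, the change variance exceeds the adjusted variance by (σ₀ − rσ₁)², which cannot be negative. The one degree of freedom spent on the slope is ignored; it is small against 65.

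**4. Where the excess comes from.** It is chance baseline imbalance. With 68/3 ≈ 23 per arm, the standard error of a baseline difference between two arms is √(2/23) = 0.29σ. An imbalance of that size shifts the change-score contrast by (1−r) × 0.29σ, in the opposite direction: 0.21σ, 0.15σ and 0.09σ at r = 0.3, 0.5 and 0.7.

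**5. Illustration.** Take a difference of 10 points (the MCID), an assumed SD of 20, two-sided 5% and 80% power. Participants per arm from the change SD and the adjusted SD are 88 v 58 at r = 0.3, 63 v 48 at r = 0.5 and 38 v 33 at r = 0.7.

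**6. Time point.** The Objectives run to the end of the intervention, which Measurements and Their Timing equates with week 6. Primary Feasibility Measurement and Statistical Analyses both say week 6. Only the responder sentence departs from this. Table 2 collects the Nepean Dyspepsia Index (NDI) at both week 6 and week 8, so the two readings would use different data.

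**The case against.** - **Feasibility purpose.** The study states that it could not be powered for an effect, and one purpose is to find which measures to carry forward. Examining several scores is part of that. This stands, and it limits the harm to selective emphasis and the choice of SD.
- **Order implied.** The plan can be read as making the unadjusted model the lead and the adjusted one secondary. The count then falls to 3 × 2 = 6 from an overall test, or 12 with two contrasts. But the lead would then be the less efficient model, and the SD point is unchanged.
- **Count.** No pairwise contrasts are named, so 24 is conditional and 12 is the figure the text supports directly. The results also overlap heavily and are not separate outcomes.
- **Oversizing is the safe direction.** It does not threaten the next trial's power. It arises only if the sponsor takes the change SD and the next trial adjusts for baseline. This stands; the cost is unneeded recruitment.
- **Score wording.** The Objectives use the plural and name both domains, so *global* may simply mean overall. That is probably the intention. One word still conflicts with its definition elsewhere.
- **A separate analysis plan may rank these.** It may settle population and model. It would not remove the two wording conflicts in this article.

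A reader might infer that the primary time point and model differ between sections. They do not: the main change is to week 6 throughout, and both models appear only in Statistical Analyses.

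**Conclusion.** The point holds as a matter of ranking and wording. The baseline-adjusted contrast has 35%, 25% and 15% less variance at assumed r of 0.3, 0.5 and 0.7, yet it is presented second. Weighted against unweighted quality of life, and ITT against per-protocol, are unranked. That leaves 12 results, or 24 if each honey arm is set against control. The oversizing factors of 1.54 to 1.18 rest on equal variances and on the assumed r.

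Two stronger readings are not supported:

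- **That the change-score SD is estimated less precisely.** With 68 participants the 95% CI factors are 0.854–1.207 unadjusted (65 df) and 0.853–1.209 adjusted (64 df). The SD is larger, not less precise; it is the treatment contrast that loses precision.
- **That the plan has an inflated confirmatory error rate.** If all 24 results were tested at 5%, treating them as independent gives a 71% chance of at least one false positive. A simulation with assumed correlations between the scores gives about 32% to 36%. But the study claims no confirmatory test, so these figures show only how much room there is for selective emphasis.

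**What to change.** 1. Make the baseline-adjusted model at week 6 in the ITT set the lead estimate for two scores: the total symptom score and the weighted quality-of-life score, which has the MCID. This leaves 2 lead results from an overall test, or 4 with two honey-versus-control contrasts.
2. Label the unadjusted, unweighted, per-protocol and responder results supportive.
3. In the Objectives, replace *global* with these two scores. In Primary Feasibility Measurement, set the responder analyses at week 6.
4. Report the adjusted residual SD and the baseline-to-week-6 correlation for future sizing.
5. Date the ranking and state whether it was set before unblinding. Results says that analysis of the patient-reported outcomes was under way in March 2024. The blinding section holds allocation closed until the primary analyses are complete, so a blinded ranking is possible but has to be documented.

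No new data or models are needed: baseline is collected and the adjusted model is already planned. The cost is a short text change and an honest, dated note. A ranking set after unblinded results were seen should be reported as post hoc.

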### Biological Measurements

#### Blood Samples

A trained phlebotomist collected fasting peripheral blood at each visit (baseline, week 2, week 4, and week 6). Blood was collected into 10-mL EDTA tubes (Becton, Dickinson and Company) for peripheral blood mononuclear cells (PBMCs) extraction, 2 EDTA tubes (4 mL each) to measure insulin, glucose, and alpha-1 acid glycoproteins levels, and 1 serum tube without clot activators (4 mL) to measure cytokine, MMP-9, lipid, and high-sensitivity C-reactive proteins concentrations. Blood samples collected in the EDTA tubes were kept in a chilled box with ice packs until processing. Blood samples collected in the serum tubes were kept at room temperature for 45 minutes to allow coagulation before processing. Vacutainers (excluding those for PBMC extraction) were centrifuged at 2200 *g* for 10 minutes at 4 ℃, and aliquots were stored at –80 ℃ until analysis.

The PBMCs were extracted using standard procedures (Multimedia Appendix 2) at the Department of Microbiology and Immunology, University of Otago, Dunedin, New Zealand, and Mātai Hāora-Centre for Redox Biology and Medicine laboratory at the University of Otago, Christchurch, New Zealand. The extracted cells were stored in liquid nitrogen until analyses at the Malaghan Institute of Medical Research (Wellington, New Zealand). Immuno-profiling of the PBMCs, including phenotypic and functional markers, will be performed using spectral flow cytometry.

Plasma cytokines including IL-1β, IL-6, IL-8, IL-10, IL-12p70, IL-17A, IL-18, IL-23, IL-33, interferon-α2, interferon-γ, TNF-α, and monocyte chemoattractant protein-1 will be measured using a cytokine bead assay (MILLIPLEX MAP Kit Human Cytokine Chemokine Magnetic Bead Panel Immunology Assay, Millipore) as per the manufacturer’s instructions at the Malaghan Institute of Medical Research (Wellington, New Zealand).

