Stool microbiome data will be analyzed using principal coordinate analysis and permutational multivariate ANOVA. Alpha-diversity and beta-diversity indices will be calculated. Differential abundance analysis of the microbiome abundance data (Analysis of Composition of Microbiomes with Bias Correction) [59] will be used to explore relationships between diet, metadata, diversity indices, and microbiome taxonomic traits. All analyses will be done in R with probability values adjusted for multiple comparisons using the Benjamini-Hochberg method [60] and data will be reported according to the reporting guidelines for human microbiome research (STORMS [Strengthening The Organizing and Reporting of Microbiome Studies]) [61].

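### The secondary-outcome paragraph sets a P≤.05 significance label and also rules out formal hypothesis testing; if the label is followed, chance immune findings can be called significant.

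*Protocol article*

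**What the plan says.** All of the conflicting text is in one paragraph of the protocol article, under Data Analysis, Statistical Analyses. It opens with the secondary outcomes and states that "changes in scores from baseline to the end of the intervention will be analyzed using appropriate statistical tests, depending on the data distribution". It then describes how results will be presented: descriptive summaries "with a 95% CI and *P*≤.05 value to show statistical significance". After a sentence on handling confounders, it closes with "No formal hypothesis testing will be conducted on these variables".

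The next paragraph, on stool microbiome data, is the only place that mentions multiplicity: "All analyses will be done in R with probability values adjusted for multiple comparisons using the Benjamini-Hochberg method".

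The Objectives section makes immune parameters a secondary objective, compared between the honey and control groups. Under Blood Samples the article names 13 cytokines and adds that "Immuno-profiling of the PBMCs, including phenotypic and functional markers, will be performed using spectral flow cytometry", without giving the number of cell markers.

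**The concern.** Applying a test and declaring significance at a fixed threshold is what most readers understand by hypothesis testing. An analyst given this paragraph is told to do that and told not to, and two analysts could report the same data differently while each citing the plan.

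The consequence is largest for the immune parameters, because many are measured at once. The study analyses 68 participants over three arms, and the Anticipated Findings section says it could not be powered to detect a treatment effect. The section on measurement timing says the results will help choose sensitive measurements for later trials. A cytokine called significant by chance could therefore influence the next design and be reported in wording that suits a confirmatory result.

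**Working it through.** **Is the conflict in the text?** Three statements stand in one paragraph on secondary outcomes: use statistical tests; use P≤.05 to show significance; conduct no formal hypothesis testing. Nothing in the paragraph assigns them to different outcomes or ranks them. The conflict therefore does not depend on a separate analysis plan that is not shown.

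**Does the Benjamini-Hochberg sentence cover the immune markers?** It sits in the microbiome paragraph and specifies R alone. The Statistical Analyses section opens by allowing R, Stata or SPSS for all statistical analyses. The R-only sentence is therefore local to the microbiome.

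**Size if the P≤.05 label is followed.** The article states no error rate for the secondary outcomes, so there is no figure to reproduce.

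Inputs:
- 13 cytokines, counted under Blood Samples.
- Three arms (Study Overview) and 68 participants analysed (Results).
- Threshold 0.05 (Statistical Analyses). Sidedness is not stated; two-sided is assumed.
- Number of tests per cytokine is not stated. Two cases are shown: one three-group test, and two contrasts of a honey arm with control.
- Correlation between cytokines is not stated. The range 0 to 0.7 is assumed.

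Expected false positives with no true effect, for m tests, are m × 0.05, whatever the correlation:
- One test per cytokine: 13 × 0.05 = 0.65.
- Two contrasts per cytokine: 26 × 0.05 = 1.3.

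Chance of at least one, if all tests are independent, is 1 − 0.95^m:
- m = 13: 1 − 0.95^13 = 0.487.
- m = 26: 1 − 0.95^26 = 0.736.

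The tests are unlikely to be independent. Cytokines on one panel tend to move together, and the two contrasts share a control arm. A simulation allowed for this, with 68 participants split 23/23/22 (assumed), equally correlated normal markers, no true effect and 4,000 runs per setting. The chance of at least one false positive was:

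| Correlation | One three-group test each | Two contrasts each |
|---|---|---|
| 0 | 48.1% | 70.7% |
| 0.3 | 42.6% | 62.7% |
| 0.5 | 34.8% | 52.0% |
| 0.7 | 24.6% | 39.2% |

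Combining the formula and the simulation, the range is about 25% to 49% for three-group tests and 39% to 74% for two contrasts. The 74% needs independent contrasts as well as uncorrelated markers; allowing for the shared control arm lowers it to about 71%.

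**Effect of the adjustment.** In the same simulation, Benjamini-Hochberg at 5% over the 13 cytokines brought the chance of any false positive to between 3.3% and 5.1% in all eight settings.

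**The case against.** The strongest reply is that the two instructions can be read together. The closing sentence follows one about confounders, so what it refers to is not fully clear. The P≤.05 phrase is attached to descriptive statistics. Nominal P values and CIs without confirmatory claims are a usual stance in a feasibility study. This has some force: it is too strong to say that the instructions can never be reconciled. But the paragraph's subject is the secondary outcomes, a descriptive mean or median has no P value of its own, and the stated purpose of the threshold is to show significance. If a softer meaning was intended, the wording does not convey it.

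A second reply is that the test paragraph speaks of changes in scores, which fits the PROMIS questionnaires best, and that blood markers have their own heading, Biological Measurements. This also has some force. However, the Objectives section lists immune parameters as a secondary objective, so they fall under the paragraph's opening words. Lipids are not named in any secondary objective and are not counted here.

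A reader might also infer that the lack of multiplicity control outside the microbiome is a defect in its own right. The document does not support that. Unadjusted exploratory analysis is acceptable in an unpowered feasibility study, and the procedure for secondary panels may be in the full protocol or analysis plan. Adjustment becomes an issue only because the text keeps a significance label.

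**Conclusion.** The concern holds as a conflict of wording with a practical consequence. The plan tells the analyst both to label secondary results significant at P≤.05 and not to test them formally. If the label is used and there is no true effect, the 13 cytokines alone give 0.65 or 1.3 expected false positives. The chance of at least one is about 25% to 49% (one three-group test each) or 39% to 74% (two contrasts each). These figures rest on the assumed number of tests, correlation range and arm sizes. The mononuclear-cell panel is left out because its size is not given, and it would add to them.

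A reader might infer that the chance of a false finding is simply 74%, or 86% if the comparison of the two honey arms is added (1 − 0.95^39). The document prescribes no pairwise contrasts, and both figures need independent tests. The third contrast is also fully determined by the other two, so 86% is not a fair estimate.

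The primary analysis of the Nepean Dyspepsia Index is not touched by any of this.

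**What to change.** Delete the P≤.05 significance label from the secondary-outcome paragraph. State that secondary outcomes will be reported as between-group differences with 95% CIs and labelled exploratory, and say explicitly which outcomes the sentence on no formal testing covers.

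If significance is still to be declared for the cytokine and mononuclear-cell panels, apply within each panel the Benjamini-Hochberg adjustment that the plan already uses for the microbiome.

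This is a change of wording. It needs no new data and leaves the primary analysis as it is. The downside is that fewer markers will be called significant. The Results section says that analyses were still under way in March 2024, so the rule should be settled before secondary results are reported.
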